## Abstract

**Background::**

Acupuncture may improve the menstrual frequency of women with polycystic ovary syndrome (PCOS). However, more sufficient data are needed to improve the efficacy of acupuncture.

**Methods::**

A total of 172 participants diagnosed with PCOS would be randomly assigned to either the acupuncture group or sham-acupuncture group, at a ratio of 1:1. Participants in both groups will receive treatment for 12 weeks, 3 times a week. The primary outcome will be the proportion of participants with at least a 50% increase from baseline in the monthly menstrual frequency from baseline after 12 weeks intervention, while secondary outcomes will be the difference in anthropometrics, serum hormone level, ovarian morphology, anxiety and depression, and quality of life from baseline to after 12 weeks intervention and to 12 weeks postintervention follow-up between groups.

**Discussion::**

The aim of this study is to evaluate the efficacy and safety of acupuncture for improving menstrual frequency and other symptoms of patients with PCOS. The limitation of this trial is that it would be difficult to blind the acupuncturists. In addition, these findings may not be suitable for women with PCOS who are seeking pregnancy.

## Introduction

1

Polycystic ovary syndrome (PCOS) is a dysfunction of endocrine system in women of reproductive age.^[1]^ Irregular menstruation (oligomenorrhea or amenorrhea), hyperandrogenism, and infertility are the common clinical manifestation of PCOS.^[2]^ The prevalence of PCOS is 6% to 21%, depending on the diagnostic criteria applied and population studied.^[3]^ Approximately 5.6% women in China have this syndrome, according to an epidemiological investigation.^[4]^ The daily life of patients with PCOS would be affected severely due to intensive mental pressure.^[5]^ Moreover, there is also a huge economic burden brought by this disease. A study is reported that 4.36 billion dollars have been spent for evaluating and providing care to reproductive-aged women with PCOS in the United States.^[6]^

As for the diagnosis of PCOS, 3 consensuses have been successively proposed by the National Institutes of Health, by both the European Society for Human Reproduction and Embryology (ESHRE) and the American Society for Reproductive Medicine (ASRM), and by the Androgen Excess Society, respectively.^[7]^ The Rotterdam criteria proposed by ESHRE and ASRM have been recommended to be used in China.^[8]^

Menstrual-related disorders, androgen-related symptoms, and infertility are the common reasons for women with PCOS who visit their doctors. There is no uniform therapeutic regimen of PCOS due to the different goals of treatment. Lifestyle intervention and weight loss should be applied as the first choice for overweight patients.^[9]^ For inducing ovulation, the first-line pharmacological treatment is clomiphene citrate, the second-line pharmacological treatment is the administration of exogenous gonadotropins or laparoscopic ovarian surgery, and the third-line treatment is high-complexity reproduction treatment such as in vitro fertilization or intracytoplasmic sperm injection.^[10]^

Hormonal contraceptives have been recommended to be used as first-line management for the menstrual abnormalities and hirsutism/acne of PCOS. Combined oral contraceptives (COCs) are a combination of low doses of synthetic estrogens and progestogens, which have been used for patients not seeking pregnancy.^[11]^ Major morbidities, including cardiovascular events related to these combined COCs, have been reported among women of reproductive age, although data remain limited for these results.^[12]^

Recently, it has been reported that acupuncture may be useful for improving ovulation rate^[13–15]^ and treating oligo/amenorrhea.^[16]^ A systematic review revealed that there was an improvement in the menstrual frequency of PCOS patients after acupuncture treatment.^[17]^ However, menstrual frequency was not used as the primary outcome, and more sufficient data would be needed to prove the efficacy of acupuncture.^[18,19]^ A sham-controlled randomized trial will be performed in this trial to evaluate the efficacy of acupuncture in improving the menstrual frequency of PCOS patients who do not have fertility requirements.

## Methods

2

### Study aims

2.1

In this study, the efficacy of acupuncture on improving the menstrual frequency in women with PCOS will be evaluated.

### Study design

2.2

This study is a prospective, randomized and sham-controlled trial. The flow chart is shown in Fig. 1 and the time point of assessment is shown in Fig. 2. The Standard Protocol Items: Recommendations for Interventional Trials (SPIRIT)^[20]^ and the Standards for Reporting Interventions in Clinical Trials of Acupuncture (STRICTA)^[21]^ guidelines were followed during the development of the protocol of this study.

**Figure 1 F1:**
[figure not shown]
The flow chart of the trial.

**Figure 2 F2:**
[figure not shown]
The time point of assessment.

### Study setting and recruitment

2.3

This study will be conducted between July 2018 and December 2019. A total of 172 participants will be recruited in Guang’anmen Hospital, China Academy of Chinese Medical Sciences, through posters, hospital webs, and networks. The research assistants will be in charge of recruitment, and a gynecologist will be in charge of the diagnosis of the participants.

### Inclusion criteria

2.4

Participants who fulfill the following criteria will be included.1.Participants meet the Rotterdam diagnostic criteria^[2]^ with oligomenorrhea or amenorrhea. (Oligomenorrhoea is defined as an intermenstrual interval of >35 days or <8 menstrual bleedings in the past year. Amenorrhea is defined as absent menstrual bleeding or no menstrual bleeding in the previous 90 days.)2.Participants who have at least 2 of the following features that meet the Rotterdam diagnostic criteria:a.Clinical or biochemical hyperandrogenism: Biochemical hyperandrogenemia is defined as a total serum testosterone concentration above normal threshold, and/or clinical hyperandrogenism is defined as a Ferriman–Gallwey (FG) score^[22]^ of ≥5^[23]^ or acne defined by the Global Acne Grading System (GAGS)^[24]^ as “mild”/ “moderate”/ “severe”/ “very severe.”b.Polycystic ovary morphology is defined as the presence of ≥12 follicles in each ovary measuring 2 to 9 mm in diameter and/or an ovarian volume >10 mL on transvaginal ultrasound.3.Participants who are between 18 and 40 years old.4.Participants who joined the research and provided a signed informed consent voluntarily.

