#### Statistical analysis

2.12.2

Data will be analyzed using SPSS software V.20.0 (IBM SPSS Statistics; IBM Corp, Somers, NY), based on the intention-to-treat (ITT) principle. Missing data will be calculated using the actual observational value instead of the method last observation carried forward. For continuous data, the data will be presented as mean ± standard deviation when normally distributed, or be presented as median (interquartile range) when not normally distributed. Statistical comparisons will be performed by Student *t* test and Wilcoxon rank sum test for continuous data and by *X*^*2*^-test for categorical data. The difference between groups will be analyzed by *X*^*2*^-test or Wilcoxon rank sum test. A *P* value <.05 will be considered statistically significant. The phenotypic distribution will be analyzed according to the included participants, and a subgroup analysis will be conducted according to these phenotypes. Moreover, the phenotypes of these participants will be divided into polycystic ovaries combined with oligo/amenorrhea and hyperandrogenism, oligo/amenorrhea and hyperandrogenism combined with polycystic, and oligo/amenorrhea combined with polycystic ovaries.

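### Inclusion criterion 2 asks for at least two of only two listed features, so read literally it admits one phenotype and contradicts the planned phenotype subgroups, whose labels also need repair

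*Protocol article*

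**What the plan says.** Section 2.4 of the Protocol article joins its inclusion criteria: "Participants who fulfill the following criteria will be included". Criterion 1 requires the Rotterdam diagnosis "with oligomenorrhea or amenorrhea. (Oligomenorrhoea is defined as an intermenstrual interval of >35 days or <8 menstrual bleedings in the past year". Criterion 2 covers "Participants who have at least 2 of the following features that meet the Rotterdam diagnostic criteria" and lists two items:

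- Item a begins "Clinical or biochemical hyperandrogenism: Biochemical hyperandrogenemia is defined as a total serum testosterone concentration above normal threshold". Clinical and biochemical forms are alternatives within this one item.
- Item b begins "Polycystic ovary morphology is defined as the presence of ≥12 follicles in each ovary measuring 2 to 9 mm in diameter". It is the last item under criterion 2.

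Section 2.12.2 turns to phenotypes: "The phenotypic distribution will be analyzed according to the included participants, and a subgroup analysis will be conducted according to these phenotypes". It then names three groups: "polycystic ovaries combined with oligo/amenorrhea and hyperandrogenism, oligo/amenorrhea and hyperandrogenism combined with polycystic, and oligo/amenorrhea combined with polycystic ovaries".

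**The concern.** The eligibility rule and the analysis describe different populations. Criterion 2 as worded makes both of its features compulsory on top of the menstrual disorder, so only one phenotype can enter. The analysis section expects several. Eligibility decides whom the primary result describes, and a rule that is read one way for some women and another way for others cannot be put right after enrolment.

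The subgroup list has a separate fault. As printed, a woman with all three features fits the first two labels equally well. A woman with oligo/amenorrhoea and hyperandrogenism but no polycystic ovaries has no label at all.

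**Working it through.** The point is logical and disputes no figure in the protocol. It does not depend on the content of the cited diagnostic consensus, only on the protocol's own two sections.

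**Inputs.** Let OA, HA and PCO equal 1 if oligo/amenorrhoea, hyperandrogenism and polycystic ovary morphology are present, and 0 otherwise.

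- Criterion 1 (section 2.4): OA = 1.
- Criterion 2 (section 2.4): at least 2 of items a and b, that is HA + PCO ≥ 2. Each term is at most 1, so this means HA = 1 and PCO = 1.
- Both criteria apply together.

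Two ways round this fail on the text. Clinical and biochemical hyperandrogenism cannot count as two features, because they sit in one item joined by *or*. OA cannot count towards the two, because it is not among the features listed under criterion 2.

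**Step 1: who can enrol.** All combinations with at least two of the three features:

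| Combination | HA + PCO | Criterion 1 | Criterion 2 as written | Enrols as written | Enrols if criterion 2 were HA + PCO ≥ 1 |
|---|---|---|---|---|---|
| OA + HA + PCO | 2 | met | met | yes | yes |
| OA + HA | 1 | met | not met | no | yes |
| OA + PCO | 1 | met | not met | no | yes |
| HA + PCO | 2 | not met | met | no | no |

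As written, 1 of 4 combinations enrols; with at least one of a and b, 3 of 4 do. The last row is excluded by criterion 1 on purpose, since the trial studies menstrual frequency, and is no part of the error. Among the three combinations with OA, criterion 2 as written admits 1 and bars 2.

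**Step 2: the subgroup labels in section 2.12.2.**

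| Label | Features named | Remark |
|---|---|---|
| First | PCO, OA, HA | three-feature phenotype |
| Second | OA, HA, and a word cut short after the adjective | as printed, the same three features |
| Third | OA, PCO | two-feature phenotype |

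The three labels name 2 distinct sets. OA + HA without PCO is missing.

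**Step 3: the two sections together.** The third label can be read in two ways.

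- It means OA and PCO without HA, as its place beside "polycystic ovaries combined with oligo/amenorrhea and hyperandrogenism" suggests. Criterion 2 bars these women and the group is empty.
- It means OA and PCO with or without HA. Every enrolled woman has all three features, so every woman falls under this label as well as the first.

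In neither case is there a contrast between phenotypes. If the second label is repaired to OA + HA without PCO, the conflict widens, because criterion 2 bars that group too and two of the three subgroups would then be empty.

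**Step 4: which reading fits.** With OA mandatory plus at least one of a and b, the three combinations that can enrol are OA + HA + PCO, OA + HA and OA + PCO. These match three subgroups once the second label is repaired.

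**The case against.** The best reply is that this is a drafting slip. Criterion 1 already invokes the Rotterdam criteria with a menstrual disorder, criterion 2 refers to the same criteria, and section 2.12.2 lists a phenotype naming only two features. Together they suggest a rule of two features in total, one being oligo/amenorrhoea, with a miscounted lead-in. That is probably right as to intent, and it is why the finding is put as a contradiction to be reconciled and not as a deliberate restriction. It does not clear the text: the rule as stated is specific, and whoever applies it literally will turn away women whom the analysis section expects.

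A second reply is that the duplicate label is damaged text. This also has force. The second label stops after *polycystic* with no noun, so a garbled oligo/amenorrhoea with hyperandrogenism group is plausible. As printed, though, the list still names one phenotype twice and leaves another out.

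A third reply is that nothing here touches the randomisation, the primary outcome, the sample size calculation or the primary test. That stands.

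Several stronger inferences are tempting but unsupported:

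- *The results could not be claimed for women with PCOS.* Women with all three features do have the syndrome. A narrow entry rule limits generalisability; it does not invalidate the result.
- *A known share of recruits would be lost.* The documents give no phenotype frequencies, so the loss cannot be sized.
- *Centres would apply the rule differently.* Section 2.3 names one hospital, with a gynaecologist in charge of diagnosis. The risk is inconsistent application by recruiting staff there.
- *The subgroup method is deficient because no interaction test is described.* That detail may sit in a statistical analysis plan that is not shown.

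**Conclusion.** The concern holds as a contradiction between sections 2.4 and 2.12.2. Taken literally, criterion 2 limits entry to one of the three phenotypes compatible with oligo/amenorrhoea and leaves the planned subgroup analysis without a comparison. The subgroup list, as printed, names two distinct groups where three are implied.

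The first part rests only on reading the criteria as jointly required and items a and b as the full list, both of which the text supports. The view that criterion 2 is miscounted, and that the second label is garbled, is an inference from section 2.12.2 that the sponsor must confirm. The effect is on who is enrolled, how far the result generalises, and whether the subgroup analysis can be done. The comparison of acupuncture with sham remains valid for the women randomised.

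**What to change.** Reconcile section 2.4 with section 2.12.2, with the sponsor stating which population was meant.

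- **If several phenotypes were meant**, which is the reading consistent with section 2.12.2: reword criterion 2 to require, besides oligo/amenorrhoea, at least one of features a and b. Replace the subgroup list with three mutually exclusive groups: (i) all three features; (ii) oligo/amenorrhoea and hyperandrogenism without polycystic ovaries; (iii) oligo/amenorrhoea and polycystic ovaries without hyperandrogenism.
- **If only the three-feature phenotype was meant**: say so in criterion 2, delete the phenotype subgroup analysis, and narrow the population named in the aims and conclusions.

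Either route is an amendment to two paragraphs (plus the aims, for the second), submitted to the ethics committee as section 2.12.5 requires. No new measurements are needed, because all three features are already assessed for eligibility. If women have already been enrolled, record which reading was applied to each.

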### Randomization and blinding

2.6

#### Randomization

2.6.1

A 2-week to 4-week baseline assessment will be needed before randomization. The randomization process will be performed by the Clinical Pharmacological Assessment Center at Guang’anmen Hospital using the Statistics Analysis System (SAS) software. The participants will be divided into 2 groups: acupuncture group and sham-acupuncture group; at a ratio of 1:1. Opaque envelopes with sequence numbers marked outside will be used for sealing the paper-written random numbers and grouping information inside. The acupuncturists will obtain the information of the random numbers and group assignment by opening these envelopes.

### Blinding

2.7

Researchers responsible for the recruitment or data collection, participants, statisticians, and other researchers who are not participants in the treatment process will be blinded.

### Intervention

2.8

#### Acupuncture group

2.8.1

Acupuncturists who have an official license and at least 2-year of clinical experience of acupuncture will perform the treatment. Bilateral ST25, EX-CA1, CV4, and SP6 will be selected for treatment. The location of the acupoints will be based on the “Nomenclature and location of acupuncture points”^[25]^ drafted in 2006 by the National Standard of the People's Republic of China (GB/T 12346–2006) and the consensus of experts. After routine sterilization of the local skin, bilateral ST25, EX-CA1, CV4, and SP 6 will be inserted by the needles (0.30 mm in diameter, 40 mm in length) (Hwato Brand, Suzhou Medical Appliance Factory, China) to a depth of 25 to 30 mm to the abdominal muscle layer with the manipulation of lifting, thrusting, and rotating until “de qi” ^[26]^ (the sensation of sourness, numbness, and heaviness). Each session will last for 30 minutes, and the manipulation of lifting, thrusting, and rotating evenly 3 times will be used for CV 4 and SP 6 every 10 minutes. If the date of treatment is during the menstrual circle, the treatment will be continued as usual. Participants will be treated 3 times a week for 12 weeks with 36 sessions.

### Sham-acupuncture group

2.9

The sham ST25, EX-CA1, CV4, and SP 6, which are 1 cun (25 mm) outward to ST25, EX-CA1, CV4, and SP 6, will be inserted to 2 to 3 mm with needles with a diameter of 0.30 mm and a length of 13 mm. The needles will be inserted without de qi or any manipulation. The treatment sessions will be the same as those in the acupuncture group.

The treatment will be discontinued for pregnant patients. After the treatment, if patients have no menstrual bleeding for 3 months, progesterone (Zhejiang Aisheng Pharmaceutical Co., Ltd., Hangzhou, Zhejiang, China ) will be taken for hormonal withdrawal bleeding. Two 200-mg tablets will be continuously taken every night for 10 days. Patients will stop taking the medicine when menstrual bleeding occurs during these 10 days.

### Outcome measure

2.10

#### Primary outcome measure

2.10.1

The proportion of participants who have at least a 50% increase from baseline in monthly menstrual frequency after 3 months of intervention.

Baseline monthly menstrual frequency was calculated through the number of menstrual bleeds in 3 months before intervention divided by 3. Monthly menstrual frequency from baseline to 3 months was calculated through the number of menstrual bleeds during the 3-month intervention divided by 3.

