#### Sample size

2.12.1

The calculation of the sample size was based on the primary outcome, which is the proportion of participants with at least a 50% increase from baseline in monthly menstrual frequency during the 12-week intervention.

According to 1 previous study,^[16]^ 38% of participants had increased menstrual frequency after 14 sessions of electro-acupuncture, and the proportion of participants with at least a 50% increase from baseline to 12 weeks was assumed to be 35% in the acupuncture group and 15% in the sham-acupuncture group. Each group sample size of 71 achieves 80% power to detect a difference between group proportions of 20%. A total of 172 participants (86 participants in each group) will be required for the study, with an alpha risk of 5% and a beta risk of 20%, assuming 20% loss to follow-up.

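### The primary responder rule cannot classify women with no bleed at baseline, although the entry criteria expressly admit them

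*Protocol article*

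**What the plan says.** Protocol article, 2.10.1 (Primary outcome measure), defines the endpoint as "The proportion of participants who have at least a 50% increase from baseline in monthly menstrual frequency after 3 months of intervention". It then fixes both terms of the ratio. For the denominator: "Baseline monthly menstrual frequency was calculated through the number of menstrual bleeds in 3 months before intervention divided by 3". For the numerator: "Monthly menstrual frequency from baseline to 3 months was calculated through the number of menstrual bleeds during the 3-month intervention divided by 3".

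Section 2.4 (Inclusion criteria) admits two menstrual categories. One is amenorrhoea: "Amenorrhea is defined as absent menstrual bleeding or no menstrual bleeding in the previous 90 days". The other is oligomenorrhoea: "Oligomenorrhoea is defined as an intermenstrual interval of >35 days or <8 menstrual bleedings in the past year".

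Section 2.11.1 reuses the 50% rule for the 3-month post-treatment follow-up and adds the change in monthly frequency as a secondary outcome. Section 2.12.1 (Sample size) bases 71 per group and 80% power on responder proportions that the article says were "assumed to be 35% in the acupuncture group and 15% in the sham-acupuncture group". Section 2.12.2 commits to intention-to-treat analysis. None of these sections says how a baseline of zero is handled.

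**The concern.** The amenorrhoea criterion and the baseline window cover almost the same period. The entry criterion itself therefore produces women with a baseline of zero, for whom the stated endpoint has no value. Oligomenorrhoeic women with a gap of more than 3 months can fall into the same group.

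Two analysts could both follow section 2.10.1 and report different primary results. If the convention is settled after outcomes are known, it could decide significance. Dropping these women would also conflict with the intention-to-treat commitment. The planned responder rates cannot be judged either, because they mean different things under different conventions.

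**Working it through.** **1. The plan's own figure.** Inputs from section 2.12.1: 35% vs 15%, alpha 5% (two-sided assumed), 80% power. The arcsine formula gives 71 per group, the stated number. The pooled normal formula gives 73 and the unpooled one 70. Power at n per group, pooled:

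power = Φ{[|p1 − p2|√n − 1.96√(2p̄(1 − p̄))] / √(p1(1 − p1) + p2(1 − p2))}

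At n = 71: (0.20 × 8.426 − 1.96 × √0.375) / √0.355 = 0.485 / 0.596 = 0.81, so power is 79%. The stated figure reproduces.

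**2. What the rule asks for in whole bleeds.** Both frequencies are divided by 3, so the divisor cancels. Response means an on-treatment count of at least 1.5 × the baseline count.

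| Baseline bleeds | 1.5 × baseline | Bleeds needed | Extra bleeds |
|---|---|---|---|
| 0 | 0 | undefined as a percentage (x/0 or 0/0); met with 0 bleeds if read as a product | – |
| 1 | 1.5 | 2 | 1 |
| 2 | 3 | 3 | 1 |
| 3 | 4.5 | 5 | 2 |

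**3. No-effect responder rate by convention.** The article gives neither the share of women at baseline 0 nor the distribution of bleed counts, so the following rests on assumed models.

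*Model A: bleeds per 3 months are Binomial(3, 0.33), independent before and on treatment.* P(0) = 0.301, P(1) = 0.444, P(2) = 0.219, P(3) = 0.036.
- Response from baseline 1 or 2: 0.444 × 0.255 + 0.219 × 0.036 = 0.121.
- Baseline 0 counted as failure: 12%.
- Baseline 0 dropped: 0.121 / 0.699 = 17%.
- Baseline 0 responds with any bleed: 0.121 + 0.301 × 0.699 = 33%.
- Baseline 0 always responds: 0.121 + 0.301 = 42%.

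*Model B: gamma renewal cycles longer than 35 days, between-woman log-SD 0.4, within-woman CV 0.35, counted over 91 days before and 84 days on treatment.*

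| Median cycle (days) | Share at baseline 0 | Failure | Dropped | Any bleed responds |
|---|---|---|---|---|
| 50 | 4% | 21% | 22% | 25% |
| 70 | 10% | 15% | 17% | 24% |
| 90 | 18% | 10% | 12% | 25% |

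The convention matters little when few women start at zero and a great deal when many do. At a 90-day median cycle it alone moves the rate from 10% to 25%.

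**4. Effect on power at 71 per group.** Illustration: 20% of women have baseline 0, and the others respond at 35% vs 15%.
- Failures: 0.8 × 35% = 28% vs 0.8 × 15% = 12%; power 67%.
- Any bleed responds, assumed 50% vs 35% among these women: 38% vs 19%; power 71%.
- Dropped, leaving 57 per group: power 70%.
- Always responders: 48% vs 32%; power 49%.

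Keeping the planned 20-point difference but moving the sham rate, with the step 1 formula: 15% vs 35% gives 79%, 20% vs 40% gives 74%, and 25% vs 45% gives (1.685 − 1.96 × √0.455) / √0.435 = 0.55, or 71%.

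**The case against.** The article is condensed and the statistical analysis plan is not shown; a convention for zero baselines is often set there. That carries weight, but section 2.10.1 does not leave the endpoint open. It states the complete formula, and the formula fails for a category named in section 2.4. Section 2.11.1 softens the gap, since an absolute change in frequency is defined at baseline 0, but that outcome is secondary. The two windows also need not coincide exactly: a woman may bleed during the 2- to 4-week baseline assessment, so not every amenorrhoeic entrant will have a count of zero.

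A reader might infer more than the documents support:

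- *That the whole responder rate is arbitrary, or the comparison biased.* For baseline 1 or more the rule is fully defined. One extra bleed being enough is what a 50% rule means with counts this small. Chance responses arise equally in both randomised arms, so they cost precision and do not favour either arm.
- *That the 15% sham rate is wrong, or that true power is 70%.* The conventions and models above fall on both sides of 15%. A sham rate of 25% corresponds mainly to the any-bleed convention.
- *That women at baseline 0 respond almost automatically.* Model B gives 86–96% with at least one bleed, but a low within-woman CV nearly forces a bleed after a long gap. A Poisson mean of 1 gives 63%, and more variable cycles give 51–71%.
- *That the on-treatment window is materially too short.* Treatment lasts 12 weeks and baseline is called 3 months, but the article uses the two terms interchangeably, and any shortfall applies to both arms.

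**Conclusion.** The point stands for women with a baseline count of zero. The primary endpoint, and the follow-up outcome that reuses it, cannot be evaluated for an expressly eligible group. This follows from sections 2.4 and 2.10.1 without any modelling.

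The size depends on assumptions. Under the cycle models used, the no-effect responder rate ranges from about 10% to 25% or more according to the convention, so the assumed 15% sham rate has no fixed meaning until one is chosen. The documents do not show that this rate is wrong or that power is any particular lower figure. The coarseness at baseline 1 or 2 is a lesser matter of noise.

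**What to change.** Before unblinding:

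1. State the responder rule in whole bleeds: baseline 1 needs at least 2, baseline 2 at least 3, baseline 3 at least 5. Add one fixed rule for baseline 0, for example a set minimum number of bleeds. At least 2 is one option; what matters is that a single rule is fixed in advance.
2. Say that women with baseline 0 stay in the intention-to-treat analysis, and apply the same rule to the follow-up outcome in section 2.11.1.
3. Count bleeds over windows of the same stated length before and during treatment.
4. Add the on-treatment bleed count, adjusted for baseline count, as a supportive analysis. It is defined for every baseline value.
5. State power at 71 per group over sham rates of 15–25%, for the rule chosen.

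The cost is wording, provided bleeding dates are recorded so that equal windows can be counted. The downside is that the stated responder rates and power may become less favourable, down to about 71% if the sham rate is 25% and the 20-point difference is kept.
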